**2.2.2 Exclusion criteria.**

Children will be excluded if they have any of the following:

a) visibly bloody diarrhoea by history or at presentation, or

b) diarrhoea for > 14 days prior to admission to hospital, or

c) known inflammatory bowel disease, cystic fibrosis, or malignancy, or

d) suspected bacterial sepsis or meningitis leading to the initiation of ceftriaxone, or

e) severe metabolic acidosis with pH<7.1 or HCO3 < 10, or

f) suspected primary urinary tract infection and a urinalysis showing pyuria or positive nitrites, or

g) suspected primary diagnosis of pneumonia with a chest x-ray showing a focal consolidative process, or

h) live in a household with another individual documented to have an enteric infection of defined aetiology, or

i) are transferred from another health centre with treatment already begun with nalidixic acid, cefotaxime, or ciprofloxacin.

Children will also be excluded if they live outside Gaborone/Tlokweng/Mmopane, if they do not have a permanent address, and if a caregiver does not have ready access to a telephone (landline or mobile). We will not be enrolling children admitted to hospital for another reason who develop nosocomial diarrhoea > 48 h subsequent to enrollment. Children who require admission to hospital because of acute diarrhoeal disease who previously had been participants will not be eligible for participation again.

**2.3 What are the planned trial interventions?**

**2.3.1 All participants.** Data to generate Vesikari scores([20](#_ENREF_20)), a validated measure of gastroenteritis severity, will be collected at enrollment, and all study participants will be weighed and measured using calibrated apparatus. Percent dehydration will be abstracted from the paediatric team admission note (subjective dehydration) and will also be calculated comparing weight nadir in hospital to weight at discharge from hospital (objective dehydration). All participants will have a rectal flocked swab taken at enrollment within 18 hours of admission. Most of these children will not be started on antimicrobials at admission, as per current Princess Marina Hospital and World Health Organization standards, excepting children with severe acute malnutrition. Rehydration procedures will be decided by the attending physician; as per Princess Marina Hospital dehydration protocols, all those with severe dehydration receive intravenous rehydration with isotonic fluids and those with mild-moderate dehydration receive WHO-standard oral rehydration solution (ORS). It is standard of care at Princess Marina Hospital to also provide zinc treatment for gastroenteritis.

**2.3.2 Rapid testing and targeted antimicrobial therapy plus probiotic therapy arm.** These participants will be started on *Lactobacillus reuteri* within 24 hours of enrollment**.** All of these participants’ rectal swabs will be processed using our novel diagnostic techniques and resulted within 48 hours. It will be recommended to the attending physician that *Shigella,* ETEC, and *Campylobacter* infections be treated with azithromycin, and *Cryptosporidium* infections be treated with nitazoxanide. It will also be recommended that antimicrobials will be started as soon as possible, preferably on the day the test results become available, and antimicrobials will be provided free of charge. Probiotic therapy will be continued until the measurement of the primary outcome, 2 months post-enrollment.

**2.3.3 Rapid testing and targeted antimicrobial therapy plus placebo therapy arm.** These participants will be started on placebo therapy within 24 hours of enrollment and will have rectal swabs processed rapidly (see 2.3.2). Placebo therapy will be continued until the measurement of the primary outcome, 2 months post-enrollment.

**2.3.3 Delayed swab testing plus probiotic therapy arm.** These participants will be started on *Lactobacillus reuteri* within 24 hours of enrollment. Rectal swabs taken from children in the ‘delayed swab result’ arms will be batched and processed after all enrollment has been completed, and management in hospital will be at the discretion of the attending physician following Princess Marina Hospital standards of care. Should the attending physician consider the diagnosis of bacterial enteritis or cryptosporidiosis based on clinical judgment, azithromycin and/or nitazoxanide will be made available. Probiotic therapy will be continued until the measurement of the primary outcome, 2 months post-enrollment.

**2.3.4 Delayed swab testing plus placebo therapy arm.** These participants will be started on placebo therapy within 24 hours of enrollment and will have rectal swabs resulted only after the conclusion of the study (see 2.3.3). Should the attending physician consider the diagnosis of bacterial enteritis or cryptosporidiosis based on clinical judgment, azithromycin and/or nitazoxanide will be made available. Placebo therapy will be continued until the measurement of the primary outcome, 2 months post-enrollment.

**2.4 Laboratory testing.** A flocked rectal swab (Copan Italia S.P.A, Brescia, Italy) will be used to acquire specimens from all study participants; these will be placed in vials containing ENAT medium (Copan Italia S.P.A.) for stabilization and transport. A stool sample will be taken from each participant (as soon as reasonably possible) and stored at -70C at the National Microbiology Laboratory; these will then be batched and sent to McMaster for assessment of faecal calprotectin levels. An aliquot of the ENAT medium will have DNA extracted using QIAgen total nucleic acid extraction columns and the extracted DNA will be subjected to amplification and detection using multiplex taqman assays targeting *Shigella* spp., *Campylobacter* spp., *Salmonella* spp., ETEC and *Cryptosporidium* spp. previously adapted by our group for use on the ABI 7500 Realtime FAST qPCR platform. The remainder of laboratory testing that is required (eg. verification of HIV status, if applicable) will be done as per current Princess Marina Hospital standards of care. A stool sample will be obtained at the 2-month follow-up visit that will be sent to McMaster for faecal enzyme measurement and calculation of the environmental enteropathy score (composite of faecal alpha-1 antitrypsin, neopterin, and myeloperoxidase).

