**2.7 What is the proposed frequency and duration of follow-up?**

The research assistant will contact the participant 7-14 days after discharge from hospital to ensure that the caregivers remember the timing of the second follow-up visit and to answer any relevant questions about the study. The research assistant will then contact the participant again 60 days after enrollment to assess the primary outcome and weigh and measure the participant, if applicable. It would be optimal to have another follow-up visit approximately 12 months after enrollment; this may not be feasible with the funds we have acquired for this project, but we will ask participants for consent to approach them should moneys become available.

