**2.11 What is the proposed sample size?**

For this pilot study, a sample of 100 participants will be adequate to evaluate the feasibility criteria.

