**2.16 Ethical considerations**

**2.16.1 Risks to the safety of participants involved in the trial.**

There should be very little risk to study participants. The use of the flocked rectal swab itself – the most invasive study procedure – should pose negligible risk; the process is very similar to that used for measuring rectal temperatures, and to date, we have acquired over 500 of these specimens without a single complication. The other risk associated with the study would be breach of confidentiality, and we will take all standard precautions to guard against that: the key document linking participant names, addresses, and other direct identifiers will be kept in a locked cabinet (and a password-protected computer) in a locked office to which only the local PI and/or study nurse will have access; the case report forms with study data will be labeled only with the study ID; and no information containing direct identifiers will ever be sent electronically. Stool samples labeled with study IDs (and no direct identifiers) will be sent to Canada for enzyme testing but no genetic testing will be done.

Probiotic therapy – the administration of viable ‘good’ bacteria to patients – is not the current standard of care in Botswana for the treatment of gastroenteritis. However, as detailed previously in this protocol, numerous studies done in both higher-income and lower-income countries have documented clinically significant improvements in presumed infectious gastroenteritis associated with probiotic use and no significant adverse reactions have been observed after treatment of thousands of immunocompetent children. Children with severe acute malnutrition are obviously not functionally immunocompetent, so they will not be eligible for probiotic treatment in this study.

It will be explained to participants that they have much to potentially gain by being in the study; should our testing detect a treatable pathogen, this information will be communicated to the attending physician in a timely manner. Furthermore, in many cases, the study will provide drug therapy free of charge to the study participant; azithromycin should be superior to nalidixic acid, currently the standard of care for the treatment of bacillary dysentery at Princess Marina Hospital.

**2.16.2 Informed consent**.

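### The delayed-testing arms have two different milestones for their swabs, and section 2.16.1 promises timely results without limiting that to the rapid arms

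*Protocol*

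**What the plan says.** Two subsections of the protocol are numbered 2.3.3. The one that matters here is delayed swab testing plus probiotic.

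- **Section 2.3.3 (delayed plus probiotic).** In a sentence worded for the delayed arms in the plural, swabs "will be batched and processed after all enrollment has been completed". This gives a laboratory time. No reporting time is given.
- **Section 2.3.4 (delayed plus placebo).** These children "will have rectal swabs resulted only after the conclusion of the study", with a cross-reference to 2.3.3.
- **Section 2.16.1 (risks to participants).** Families will have it explained to them that "should our testing detect a treatable pathogen, this information will be communicated to the attending physician in a timely manner". No arm is named or excepted.
- **Section 2.3.2 (rapid testing), the contrast.** Here the "rectal swabs will be processed using our novel diagnostic techniques and resulted within 48 hours".
- **Section 2.7 (follow-up).** The research assistant will "contact the participant again 60 days after enrollment to assess the primary outcome". The same section adds: "It would be optimal to have another follow-up visit approximately 12 months after enrollment". That later visit is unfunded.

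No section says when, or whether, a delayed-arm result goes to a clinician or family. None expressly bars release before the 60-day assessment.

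**The concern.** In the rapid-versus-delayed comparison, the timing of the test result is the randomised intervention. The control condition is therefore defined by when its results become available, and the protocol does not fix that date in one place.

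The close of enrolment and the end of the study are different dates, because the last child enrolled still has 60 days of follow-up to run. If the batch is assayed at the first date and nothing clearly governs release, a result on a late-enrolled control child can reach the ward or the family while that child's outcomes are still accruing. Any resulting change in care would tend to make those children resemble the rapid arms. Whether a child is exposed would depend only on how late the child was enrolled.

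The outcomes open to this are those in section 2.8.2 that run to day 60: weight and height z-scores, stunting, recurrence, re-presentation, readmission and the enteropathy score.

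The 2.16.1 sentence is a separate difficulty. It describes to all families something that only the rapid-testing arms are designed to receive.

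**Working it through.** The protocol gives no figure for this overlap, so there is none to reproduce. The first step compares the text; the second sizes the overlap.

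**1. The three statements compared**

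| Section | What is timed | Milestone | Arms covered |
|---|---|---|---|
| 2.3.3 (delayed plus probiotic) | processing | enrolment complete | both delayed arms |
| 2.3.4 | resulting | study concluded (undefined) | delayed plus placebo |
| 2.16.1 | communication to the physician | timely | not restricted |

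Rows 1 and 2 differ by at least 60 days for the last child enrolled if the study's conclusion includes the 60-day assessments. If it were taken to include the possible 12-month visit, the gap would be about a year. Row 3 is incompatible with both for delayed-arm children: honouring it would mean assaying their swabs promptly, which leaves no contrast with the rapid arms.

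**2. Children still in follow-up when enrolment closes**

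Inputs:
- N = 100 (section 2.11).
- Allocation 1:1:1:1 (section 2.5), so about 50 children in the two delayed arms.
- Accrual over 9 months, 274 days (section 2.12), or over the 12-month study period, 365 days (section 2.10).
- Follow-up of 60 days (section 2.7).
- Positivity of 35%, from section 1.1, which reports a treatable pathogen in over 35% of children admitted with gastroenteritis in 2011.
- Assumption: uniform accrual.

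Formula: delayed-arm children exposed = 50 × (60 − lag) / accrual days, where lag is the time from close of enrolment to an available result.

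| Accrual | Lag | Calculation | Delayed-arm children exposed |
|---|---|---|---|
| 274 days | 0 | 50 × 60/274 | 10.9, about 11 (22%) |
| 365 days | 0 | 50 × 60/365 | 8.2, about 8 (16%) |
| 274 days | 14 days (assumed) | 50 × 46/274 | 8.4 |
| 365 days | 14 days (assumed) | 50 × 46/365 | 6.3 |
| 274 days | 30 days (assumed) | 50 × 30/274 | 5.5 |
| 365 days | 30 days (assumed) | 50 × 30/365 | 4.1 |

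Positives with no lag: 10.9 × 0.35 = 3.8, and 8.2 × 0.35 = 2.9.

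With no lag, the exposed children have on average about 30 days of follow-up left. For 9-month accrual that is 11 × 30 = 330 of 50 × 60 = 3,000 control child-days, or 11%.

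**3. After reconciliation**

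If no delayed-arm result is released until the last 60-day assessment is done, 0 of about 50 children can have one returned during 60-day follow-up.

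**The case against.** The strongest reply is that 2.3.3 and 2.3.4 can be read together: assay the batch once enrolment closes, report at the end of the study. Section 2.3.3 gives only a processing time, 2.3.4 says results come only at the end, and the recommendation to treat on a result appears only for the rapid arms. On that reading no control child has a result returned during follow-up. This is a fair reading and may be the intended one. But the protocol does not state it, the word carrying the restriction stands only in the placebo arm's subsection, and 2.16.1 points the other way.

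Three stronger readings are tempting, and the documents do not support them.

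- **That the control is contaminated by design.** No section orders release of delayed-arm results during follow-up. It would take prompt assay at the close of enrolment, disregard of 2.3.4, and application of 2.16.1 to the delayed arms. It is a permitted risk only.
- **That all 50 delayed-arm children are exposed under batch processing.** Section 2.12 cites a current flow of 4 children a day, most of them eligible. At just over 2 a day, 100 children would accrue in under 50 days. But 4 a day for 274 days is 1,096 children, so that flow does not fit the protocol's own plan of 100 within 9 months. It should not be used to size the problem.
- **That caregivers consent on a false promise.** The consent form is not among the documents, and section 2.16.2 says the trial will be explained in detail. What can be said is that the protocol's own account of the explanation lacks an arm qualifier.

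It is also right that a result from an admission swab, returned weeks later, does not recreate a 48-hour result. Finally, the trial is a pilot, justified only in that "a sample of 100 participants will be adequate to evaluate the feasibility criteria". That lowers the severity but does not remove the inconsistency.

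**Conclusion.** The point holds as an inconsistency that needs to be reconciled. Sections 2.3.3 and 2.3.4 give different milestones for the delayed arms, the later one is undefined, and the 2.16.1 statement does not hold for about half of the participants.

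The risk from the batch timing is limited: about 11 of 50 control children on 9-month accrual or 8 of 50 on 12-month accrual, with about 4 or 3 positive. These figures assume uniform accrual, no assay lag and the 35% positivity of the 2011 series; any lag reduces them. The effect on 60-day mortality would be limited, and length of stay, in-hospital fever days and 7-day mortality would be almost untouched, because late results arrive after those outcomes are largely settled.

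The 2.16.1 wording is potentially the larger matter, since applied literally it removes the comparison altogether.

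Severity is moderate. The feasibility aims do not turn on this, but section 1.2 says all aspects of the follow-up trial will be assessed, and a control condition without a fixed definition would carry into it.

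**What to change.** Reconcile sections 2.3.3 (delayed plus probiotic), 2.3.4 and 2.16.1:

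1. State one time for resulting and releasing delayed-arm swabs, in the same words for both delayed arms. Assay timing may be stated separately, since control of release is what protects the comparison.
2. Define the study's conclusion relative to the last participant's 60-day assessment, so that the contrast 2.3.4 already intends is preserved, and say whether the possible 12-month visit counts.
3. Make the explanation in 2.16.1 arm-specific, so that caregivers are told which arms receive timely results and which do not.
4. Correct the duplicate 2.3.3 numbering so that the cross-reference in 2.3.4 points to one place.

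How any result is acted on clinically, and the attending physician's discretion in the delayed arms, are for the investigators and are not touched by this.

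The cost is protocol wording, matching wording in the explanation to families, and possibly later reporting of the batch. No extra participants, visits or assays are needed.

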**2.5 What are the proposed practical arrangements for allocating participants to trial groups?**

A statistician independent of the study will generate a randomization list such that participants can be assigned at random to one of the four study groups in a 1:1:1:1 ratio. The randomization code will be generated by a random number generator and will be blocked (randomly in groups of 4-8), with the random blocking not disclosed. Given the substantial increase in mortality among children with severe acute malnutrition, randomization will be stratified by its presence or absence. Randomization will be communicated to the research assistant using an internet-based system.

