**2.2 What is the population under study?**

**2.2.1 Inclusion criteria.**

Children aged 3 to 60 months admitted to the Princess Marina Hospital paediatric medical ward primarily because of acute diarrhoeal disease will be eligible. Acute diarrhoeal disease will be defined as at least three watery stools in the 24 hours preceding admission to hospital. Children with HIV infection will not be excluded. Children with severe acute malnutrition will be eligible to be included in the rapid vs delayed testing and targeted treatment arms, but will not be randomized to probiotic (or placebo).

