**2.13 What is the proposed type of analysis?**

The principal analysis will be intention-to-treat, i.e. all participants will be analyzed in the groups to which they were randomized, regardless if they received the appropriate antimicrobials (for those in the rapid swab analysis groups) or if they were adherent to the probiotic treatment (for those in the relevant groups). As the primary outcome (mortality) is binary, the chi-square test will be used. The chi-square test will also be used to interpret the following secondary outcomes: presence of stunting at 60-day followup, 7-day mortality, recurrence of acute diarrhoea during the 60-day followup period, re-presentation to a medical professional or readmission to Princess Marina Hospital because of acute diarrhoea in the 60-day followup period, and detectable HIV viral load within 6 months of enrollment. Analysis of covariance or logistic regression will be used to analyze the following secondary outcomes: height z-score at 60 days adjusted for initial height, weight z-score at 60 days adjusted for initial weight, and environmental enteropathy score at 60 days. Survival analysis will be used to analyze the following secondary outcomes: length of stay in hospital, number of days with at least three watery stools, and number of days of fever in hospital. Secondary analyses will attempt to control for the time to initiation of appropriate antimicrobial therapy and the time to initiation of probiotic therapy. Statistical analysis will be conducted using STATA 11.0 (College Station, TX).

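### The single four-group 1:1:1:1 randomisation list, stratified by severe acute malnutrition, conflicts with the rule that malnourished children are not randomised to probiotic or placebo

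*Protocol*

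**What the plan says.** Protocol 2.1 describes a 2x2 factorial pilot in which eligible children go to one of four arms: rapid or delayed stool testing, each with probiotic or with placebo. The arm descriptions in 2.3 define those four arms and no testing-only arm.

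Section 2.5 specifies the list: "participants can be assigned at random to one of the four study groups in a 1:1:1:1 ratio". Referring to SAM, it adds that "randomization will be stratified by its presence or absence". Blocks are random, with sizes given as 4-8.

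Section 2.2.1 treats SAM children differently. It says: "Children with severe acute malnutrition will be eligible to be included in the rapid vs delayed testing and targeted treatment arms", and then rules out randomising them to either probiotic or placebo. Section 2.16.1 explains that they are not functionally immunocompetent, "so they will not be eligible for probiotic treatment in this study".

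Section 2.13 makes the principal analysis intention-to-treat: "all participants will be analyzed in the groups to which they were randomized", regardless of adherence to the probiotic. Section 2.14 says only that a separate analysis of the SAM group will be attempted.

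**The concern.** Section 2.5 does not merely overlook SAM children. It names them, gives them a stratum, and then offers that stratum only groups that include probiotic or placebo. An independent statistician building the list from 2.5 would produce four-group sequences for both strata, and the web system would issue a probiotic or placebo assignment to children who, under 2.2.1 and 2.16.1, should have none.

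Two things are at stake. First, the allocation instruction contradicts an exclusion that 2.16.1 states on safety grounds. Second, if site staff withhold the product but the four-group label stays in the database, 2.13 as worded counts those children in a probiotic or placebo group that they did not in practice enter. Testing the randomisation procedure for the later trial is one of the pilot's stated purposes (1.2), so the ambiguity could carry forward.

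**Working it through.** **Step 1: the sections side by side.**

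| Section | Who | Allocation |
|---|---|---|
| 2.1 | eligible children | four arms, each with probiotic or placebo |
| 2.5 | participants, SAM as a stratum | four groups, 1:1:1:1 |
| 2.2.1 | SAM children | rapid versus delayed only; neither probiotic nor placebo |
| 2.16.1 | SAM children | not eligible for probiotic |

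The first two rows cannot both be followed with the last two once a SAM child is enrolled. Stratifying balances the four groups within SAM; it does not remove the probiotic factor from that stratum.

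**Step 2: the planned layout.** Inputs: N = 100 (2.11) and the ratio 1:1:1:1 (2.5). Then 100/4 = 25 per group, and 50 versus 50 on each factor. Section 2.11 gives no power or precision calculation to reproduce.

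**Step 3: the layout under 2.2.1.** Let s be the SAM share. The protocol does not give it; 5-30% is assumed. Each non-SAM factorial group has 100(1 - s)/4 children, each side of the probiotic comparison has 100(1 - s)/2, and each SAM testing group has 100s/2.

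| s | per non-SAM group | probiotic v placebo | total in that comparison | SAM rapid v delayed |
|---|---|---|---|---|
| 5% | 23.75 | 47.5 v 47.5 | 95 | 2.5 v 2.5 |
| 10% | 22.5 | 45 v 45 | 90 | 5 v 5 |
| 20% | 20 | 40 v 40 | 80 | 10 v 10 |
| 30% | 17.5 | 35 v 35 | 70 | 15 v 15 |

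Rapid versus delayed remains 50 versus 50 throughout, since 100(1 - s)/2 + 100s/2 = 50. The layout of 25 per group, with 100 children in the probiotic comparison, arises only if no SAM child is enrolled.

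**Step 4: the literal list.** Two of the four groups contain probiotic, so 100s/2 SAM children would be labelled probiotic: on average 2.5 at s = 5% and 15 at s = 30%.

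**Step 5: dilution if labels are kept but no product is given.** SAM risk is then the same under both labels. On the risk-difference scale, the observed difference is (1 - s) times the difference in non-SAM children, so 95% down to 70% of its size at s = 5-30%. This needs no mortality assumption.

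For the relative risk, the protocol supplies no mortality figures for the two strata. As an illustration, assume 3% in non-SAM children on placebo, 10-20% in SAM children, and a true relative risk of 0.50 in non-SAM children:

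observed RR = [(1 - s) × 0.015 + s × m] / [(1 - s) × 0.03 + s × m], where m is SAM mortality.

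- s = 10%, m = 10%: 0.0235/0.0370 = 0.64
- s = 10%, m = 20%: 0.0335/0.0470 = 0.71
- s = 20%, m = 10%: 0.0320/0.0440 = 0.73
- s = 20%, m = 20%: 0.0520/0.0640 = 0.81

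**The case against.** The best defence is that the specific rule governs the general one. Sections 2.2.1 and 2.16.1 state the restriction plainly, SAM children already have their own sequence through stratification, and two of the four groups are rapid and two delayed. Ignoring the probiotic half of the label would give a valid 1:1 testing allocation. This stands as a workaround, so a reader who infers that SAM children cannot be allocated at all goes too far. But the protocol does not state the workaround, and 2.5 tells whoever builds the list to do something else.

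A reader might also infer that the intention-to-treat analysis is itself wrong. It is not. A child who was never randomised on the probiotic factor has no probiotic or placebo group, and the sentence in 2.13 then leaves that child out of the contrast. Dilution arises only if the child carries a four-group label. An analysis plan not shown here could also define the set for each contrast, though it could not repair the allocation text.

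Another tempting reading is that untreated SAM children would be pooled with placebo, confounding the comparison by malnutrition. No section plans this, and 2.2.1 excludes them from placebo as well. Nor does the protocol rank mortality predictors; it says only that mortality is much higher in SAM.

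On block sizes, one might infer that 5, 6 and 7 will be used, none of which can hold equal numbers of four groups. The text may equally mean blocks of 4 and 8. This needs clarifying but is not an established error.

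Finally, this is a feasibility pilot. None of the seven criteria in 2.10 depends on the probiotic mortality contrast, and 100 children will support little inference on mortality. That limits the consequence for the pilot's results, but not the need for an allocation instruction that agrees with the eligibility rules.

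**Conclusion.** The allocation text is wrong as written: 2.1 and 2.5 contradict 2.2.1 and 2.16.1 for SAM children, and nothing elsewhere in the protocol resolves it. This conclusion needs no assumed figure.

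Its size depends on the SAM share, which the protocol does not give. At an assumed 5-30%, the probiotic comparison properly contains 95 down to 70 of the 100 children, and rapid versus delayed is unaffected. The dilution of the probiotic contrast is conditional on SAM children keeping a four-group label without receiving product. The relative-risk figures above also rest on assumed mortality and only illustrate the direction and rough scale. No view is taken on whether SAM children should receive probiotic. The point is that the sections must agree before the list is generated.

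**What to change.** Reconcile 2.1, 2.5 and 2.13 with 2.2.1 and 2.16.1. If 2.2.1 and 2.16.1 stand:

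- In 2.5, specify two lists: non-SAM children to four groups 1:1:1:1, with block sizes that are multiples of 4; SAM children to two groups 1:1, rapid versus delayed, with even block sizes.
- In 2.1, describe the design to match: factorial for non-SAM children, and a testing comparison only for SAM children.
- In 2.13, state that probiotic is compared with placebo only among children randomised to that factor, and rapid with delayed testing among all children. Intention-to-treat then applies to both comparisons.

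The cost is a wording amendment and a second randomisation list. No patients are added.
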